### Recruitment of patients

The sonographers thus validated wishing to participate in the recruitment of patients will undertake to systematically perform, in any primiparous patient, a Doppler ultrasound of the uterine arteries during the first trimester ultrasound. Patients selected in this way will be referred to the nearest investigation centre.

# Course the study

### Patient selection

Sonographers who have validated their EPP will therefore systematically perform a Doppler ultrasound of the uterine arteries in any primiparous patient during the first trimester ultrasound.

In the event of bilateral notching (grade ≥ 2) and/or high pulsatility index (lowest PI value ≥ 1.7), the sonographer will inform the patient of the existence of a trial and will give her:

- a note on the trial,
- the telephone number of the investigation centre to contact,
- a duplicate of the Doppler images of each uterine artery so that the presence of bilateral notching and/or high pulsatility index can be validated by the physician or midwife performing the inclusion visit.

### Inclusion visit

Within each investigation centre, a secretariat (single phone number) will be responsible for responding to patient calls and planning inclusion visits.

At the inclusion visit, the patient will be seen by an investigator: physician or midwife.

After giving the information and answering any questions the patient may still have about the study, the investigator will need to obtain her consent. This document must be dated and signed by the patient and the investigator at this visit before any study-specific evaluation.

Collection of the medical information provided during this consultation (interrogation and standard clinical examination) and by the Doppler images will then serve to validate precisely the study's inclusion and non-inclusion criteria.

Patients having signed a consent and who meet these criteria can thus be included in this study.

Once included, the patient will be randomised to one of the 2 groups using the electronic case report form (see §8.1.2.1). At the end of this randomisation process, a specific prescription with a treatment number (Kardegic® or placebo) will be issued to the patient so that she can collect the entire treatment (161 sachets) for the entire pregnancy from the hospital pharmacy of the centre.

The patient will also be given a card specifying her participation in the study and the contact details necessary for the unblinding request, as well as a "patient" notebook to be returned to the address of the investigation centre after delivery.

### Subsequent follow-up of pregnancy

Subsequent pregnancy follow-up will be carried out according to the usual methods of pregnancy monitoring [HAS]. For a patient followed within the investigation centre itself, the data will be collected from her medical record and the "patient" notebook. For patients not falling into this situation, data will be collected via telephone calls made to the patient and the physician who followed the pregnancy.

## Rules for permanent or temporary discontinuation

### Discontinuation of participation

Patients will be able to withdraw their consent and request to leave the trial at any time and for any reason. In the event of premature discontinuation, the investigator must document the reasons as fully as possible.

The investigator may temporarily or permanently discontinue a patient's participation in the trial for any reason that would be in the best interests of the patient, particularly in the event of serious adverse events.

In the event of a patient lost to follow-up, the investigator will make every effort to resume contact with her and to determine the reasons for the loss of her follow-up.

### Termination of part or all of the research

The study may be terminated prematurely in the event of the occurrence of unexpected serious adverse events requiring a review of the safety profile of the product. Likewise, unforeseen events or new information relating to the product, in view of which the objectives of the study or clinical programme are unlikely to be achieved, may cause the sponsor to prematurely discontinue the study.

The Tours Regional University Hospital reserves the right to interrupt the study at any time if it turns out that the inclusion objectives have not been achieved.

In the event of premature termination of the study, the information will be sent by the sponsor within 15 days to AFSSAPS and the IEC.

### Follow-up modalities for a patient leaving the study

The withdrawal of a patient from the study will not change the usual methods of pregnancy monitoring [HAS]. In the event of an adverse event, whether serious or not, precise follow-up may be considered depending on the seriousness of the adverse event and the severity. The Supervisory Committee will specify the modalities for follow-up on a case-by-case basis.

# Treatments given to patients taking part in the research

## Description of the treatment(s) required to carry out the research

### Experimental medicinal product(s)

#### Identification of treatments

Women in the experimental arm will receive sachets of Kardegic® 160 mg/day. The treatment comes in the form of sachets containing 288 g of DL-lysine acetylsalicylate powder (corresponding to an equivalent of 160 mg of aspirin) to be dissolved in water.

The women in the control arm will receive sachets of an aspirin placebo (see technical offer from Bertin Pharma), which they will take according to the same dosage regimen as that defined for the experimental group.

#### Packaging and labelling

The treatments will be packaged in the form of a kit of 161 sachets.

The treatments will be packaged in order to conform to blinding and they will be labelled in accordance with Article 7 of the decree of 24 May 2006 laying down the content of the labelling of investigational medicinal products.

#### Manufacturing and distribution of treatments

Placebo manufacture and packaging along with that of Kardegic will be carried out by the contractor BERTIN Pharma.

The Internal Pharmacy (IP) of the Bretonneau Hospital of the Tours University hospital will coordinate the IPs for the recruiting centres and in particular their supply.

Each IP will then be responsible for the treatment of the patients included in their centre: delivery, management and accounting of returns, destruction and request for resupply.

#### Administration

The dosage regimen is 1 sachet/day. Treatment will be initiated at enrolment and in any case at a gestational age ≤ 15 WA completed. In the absence of intolerance or major side effects, it will be continued up to 34 WA.

#### Dosage regimen adaptation

Not applicable

#### Precautions for use

The precautions for use are described in the Kardegic® Summary of Product Characteristics (SPC).

Patients will also be advised to take this treatment in the evening during their meal [42].

## Medicinal products and treatment authorised and prohibited under the protocol

Since this is a pragmatic trial, the concomitant treatments authorised are the usual treatments.

For most teams, performing amniocentesis does not require the interruption of low-dose aspirin therapy. For this reason, there will be no unblinding for this type of procedure if an indication is made during treatment. However, it is recommended, as a precautionary measure, in this case, to avoid transplacental passage of the amniocentesis needle.

## Method of monitoring compliance with treatment

Compliance will be evaluated from the accounting of the treatments provided. For this, patients will be asked to return their treatment boxes at the time of childbirth or during a monitoring consultation after discontinuation of treatment (after 34 WA).

## Storage conditions for investigational medicinal products

### Description of storage

Each of the IPs will store the medicinal products in a specific "Clinical Trials" room, separate from the storage of the other medicinal products. Medicines will be stored in a dry place, at a temperature below 25°C and their expiry date will be observed.

## Stock management, replenishment

The stocks will be managed by the IP of the Bretonneau Hospital of the Tours University hospital. An initial allocation will be set up in the IPs of the recruiting centres.

Each of the pharmacies will be replenished according to the inclusions made by each of the centres.

# Statistical considerations

## Number of patients to include

The population size is calculated as follows:

- pre-eclampsia occurs in 5-7% of primiparous women [19]
- the presence of bilateral notching and/or a high pulsatility index is predictive of the occurrence of pre-eclampsia, and this with a sensitivity of 75% and a specificity of 67% [28]

Hence, based on these data, out of every 100 primiparous women, the following numbers are expected to occur:

|  | Pre-eclampsia | No pre-eclampsia |  |
| --- | --- | --- | --- |
| Bilateral notching and/or high PI | 4.5 | 31 | 35.5 |
| No bilateral notching | 1.5 | 63 | 64.5 |
|  | 6 | 94 | 100 |

Thus, out of every 100 primiparous women, 35.5 women are expected to present with bilateral notching and/or a high pulsatility index, of which 4.5 will go on to develop pre-eclampsia.

The expected rate of pre-eclampsia in the control group is therefore 4.5/35.5 or 12.7%.

- Hypotrophy, defined by a birth weight ≤ 5th percentile, occurs more frequently in primiparous than in multiparous women [40]. Thus, although intrinsically (probabilistic definition of the disease), the prevalence of hypotrophy as defined is 5%, in primiparous women a rate of hypotrophy of approximately 7% is expected [43].
- the presence of bilateral notching and/or a high pulsatility index is predictive of the occurrence of hypotrophy, and this again with a sensitivity of 55% and a specificity of 67% [28].

Hence, based on these data, out of every 100 primiparous women, the following numbers are expected to occur:

|  | Hypotrophy | No hypotrophy |  |
| --- | --- | --- | --- |
| Bilateral notching and/or high PI | 3.85 | 31 | 34.85 |
| No bilateral notching | 3.15 | 63 | 66.15 |
|  | 7 | 94 | 100 |

Hence, out of every 100 primiparous women, 34.85 women with bilateral notching and/or a high pulsatility index are expected, of which 3.85 will give birth to a hypotrophic child.

The expected rate of hypotrophy in the control group is therefore 3.85/34.85 or 11.0%. Moreover, it is expected that for 20% of women developing pre-eclampsia we will also observe hypotrophy.

Thus, in the control group, we expect to observe [12.7 + (11.0-0.2*12.7)] or 21.2% of events (i.e. pre-eclampsia or hypotrophy).

Our hypothesis is that aspirin will reduce the occurrence of events by 15% [32]. The expected difference is therefore 3.2%, i.e. 21.2% of events are expected in the control group compared to 18.0% in the experimental group.

Considering the risks of type 1 and 2 errors set at 5 and 20% respectively, we must include 2415 women per group (nQuery Advisor® 6.0).

Additionally, this study plans to carry out intermediate analyses. The hypotheses relating to the control group are poorly documented, which led us to rule out a triangular test experimental design. Indeed, we know that pooradvance knowledge of the success rate in the control group is potentially deleterious for the study (Sebille *et al*, Impact of a mis-specification of the response rate under standard treatment in sequential clinical trials. [*Fundam Clin Pharmacol*.](javascript:AL_get(this, 'jour', 'Fundam Clin Pharmacol.');) 2005;19:569-578). Finally, we decided to plan this study according to a Peto scheme (Peto R, Pike MC, Armitage P. Design and analysis of randomized clinical trials requiring prolonged observation of each patient. Br J cancer 1976;34:585-612. PMID).

Four intermediate analyses are planned, such that if the trial is discontinued after one of these intermediate analyses, the success rates associated with each of the groups are still accurately estimated. These intermediate analyses will be carried out every 1000 inclusions.

Carrying out an intermediate analysis leads to an increase in the total number of subjects to be included (if the study goes to its conclusion), such that the overall type I error (i.e. taking into account all the analyses) remains at the nominal value. Considering alpha at 5% and beta at 20%, the inflation parameter is 1.024 (Jennison *et al* (2000). Group sequential methods with applications to clinical trials. Chapman & Hall/CRC: Boca Raton), which leads us to include 2415*1.024 or 2473 patients per arm.

Finally, it is expected that for 0.5% [40] of women, the pregnancy will not be carried to term (medical termination of pregnancy). These women will not be taken into account in the primary analysis. We must therefore increase the number such that at the end of the study, we have 2473 analysable women per arm. This therefore leads us to include 2473/0.995 or 2486 women per arm.

Ultimately, 4972 women are expected to be included in this trial.

## Description of samples at inclusion

The randomisation groups will be compared using descriptive statistics. No statistical tests will be performed.

## Primary endpoint analysis

Rates of pre-eclampsia during pregnancy or birth weight ≤ 5th percentile will be compared using a chi-square test. An adjustment for stratification factors will also be made as part of a logistic regression model.

Intermediate analyses (one every 1000 inclusions) will be performed at the thresholds of 0.001 and 0.049 for the last one (Peto rule).

The final analysis (if it needs to be carried out) will be conducted at the end of the 4972 inclusions. It will be performed at the 0.049 threshold, which means that a significant difference will be concluded only if the degree of significance is less than 0.049.

Finally, because intermediate analyses will be carried out, it will be necessary to adjust the estimates of the effect, the confidence interval of this effect, and the degree of significance. This will be achieved through implementation of the Lan & De Mets method (Discrete sequential boundaries for clinical trials. *Biometrika*. 1983;70:659-663).

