### Description of measures taken to reduce and avoid bias

#### Randomisation

Patients will be randomised to one of the following 2 groups: the low-dose aspirin (160 mg/day) experimental group or the placebo group.

This randomisation will be stratified by investigating centre.

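### Randomisation is stratified by centre, but the apparent main test of the primary endpoint ignores centre, and the protocol does not say which of its two analyses carries the 0.001 and 0.049 thresholds

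*Protocol*

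**What the plan says.** Section 8.1.2 (Randomisation) names one stratification factor: "This randomisation will be stratified by investigating centre".

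Section 12.4 (Primary endpoint analysis) plans two analyses of the primary endpoint. The rates of the composite "will be compared using a chi-square test. An adjustment for stratification factors will also be made as part of a logistic regression model".

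The same section sets the thresholds: 0.001 at each interim analysis and 0.049 at the end, where "a significant difference will be concluded only if the degree of significance is less than 0.049". It also requires the effect estimate, its confidence interval and the p-value to be adjusted for the interim looks by the Lan and DeMets method. Neither instruction says which analysis it applies to.

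Section 12.2 calls the per-protocol analysis secondary. Section 12.5 lists the secondary analyses and does not include the centre-adjusted model. Both analyses therefore stand under the primary endpoint heading without a rank.

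**The concern.** Stratifying by centre balances the arms within each centre, so differences between centres no longer add to the variation of the treatment comparison. A chi-square that ignores centre still counts those differences in its variance. If centres differ in event rate, the variance is too large and the test is conservative. The trial has organised its randomisation to gain this precision, and the apparent main test does not use it.

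The second problem is specification. One threshold rule and one interim adjustment have to serve two analyses at up to five looks (four interim, one final). The two also estimate different things: the chi-square compares crude rates, while the logistic model gives an odds ratio conditional on centre. The p-value that decides, and the effect that is reported with an adjusted interval, should each be fixed in advance.

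**Working it through.** **1. The plan's own figure.** Section 12.1 assumes "21.2% of events are expected in the control group compared to 18.0% in the experimental group" and concludes: "Considering the risks of type 1 and 2 errors set at 5 and 20% respectively, we must include 2415 women per group". The unstratified two-proportion formula, two-sided and without continuity correction, has mean rate 0.196 and difference 0.032:

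n = [1.960 × √(2 × 0.196 × 0.804) + 0.8416 × √(0.212 × 0.788 + 0.18 × 0.82)]² / 0.032² = (1.1003 + 0.4721)² / 0.001024 = 2.4725 / 0.001024 = 2414.6, so 2415.

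This is an exact match. Then 2415 × 1.024 = 2473, 2473 / 0.995 = 2486, and 2 × 2486 = 4972. The sample size was therefore computed for a test that ignores centre.

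**2. Why the tests differ.** With 1:1 balance inside every centre, both tests have the same numerator. Only the variance differs. The chi-square uses p̄(1 − p̄); the stratified test uses the average of p_k(1 − p_k) over centres k, which is smaller by the between-centre variance of p_k. For a logit-scale SD of s, that variance is roughly [0.212 × 0.788 × s]², so the chi-square overstates the variance by a fraction of about 0.212 × 0.788 × s².

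At s = 0.4 the fraction is 0.167 × 0.16 = 0.027. Rejecting at the 0.049 critical value of 1.969 with the chi-square is then like demanding 1.969 / √(1 − 0.027) = 1.995 of the stratified statistic. That gives a size of about 4.6%.

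**3. Simulation.** Inputs:
- 14 centres in proportion to the forecasts in section 19 (78 to 260 women a year, 2,626 in all)
- 2,473 analysable women per arm, balanced 1:1 within centre
- control rate centred at 21.2%, and the odds ratio that takes 21.2% to 18.0%
- one look at two-sided 0.049
- 40,000 trials per setting

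The centre-stratified Mantel-Haenszel test represents both the proposed test and, approximately, the centre-adjusted logistic model. The SD is an assumption; the second column shows what it means around a 21.2% rate.

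| SD (logit) | 95% range of centre rates | Size, plain | Size, stratified | Power, plain | Power, stratified | Disagree, null | Disagree, alternative |
|---|---|---|---|---|---|---|---|
| 0 | none | 4.9% | 4.8% | 80.3% | 80.3% | 0.01% | 0.01% |
| 0.2 | 15–28% | 4.9% | 4.9% | 80.6% | 80.8% | 0.07% | 0.17% |
| 0.4 | 11–37% | 4.5% | 4.8% | 79.8% | 80.5% | 0.26% | 0.64% |
| 0.6 | 8–47% | 4.4% | 5.1% | 79.1% | 80.6% | 0.65% | 1.5% |
| 0.8 | 5–56% | 3.8% | 4.8% | 77.1% | 79.9% | 1.0% | 2.7% |

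The Monte Carlo standard error is about 0.1 point for size (√(0.049 × 0.951 / 40,000)) and 0.2 point for power. Read across a row rather than down: the mean event rate drifts up a little as the SD grows.

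**4. Taking the better of two p-values.** At every SD of 0.2 or more, each disagreement was the stratified test rejecting where the chi-square did not. Declaring success if either test rejects therefore has the stratified test's own size, at most 5.1% here and within simulation error of 4.9%.

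**The case against.** The strongest reply is that the protocol does indicate which test decides. The chi-square comes first, the logistic model is introduced as something done in addition, and the sample size reproduces exactly from the unstratified formula. The 0.049 rule is also attached to the final analysis in the singular. On this reading there is a main test and an adjusted companion, and any remaining ranking can be left to the analysis plan that section 12.2 refers to, which is not shown. The indication is fair, and I treat the chi-square as the apparent main test. But the section does not state the ranking, and the mismatch between the randomisation and that test is in what the protocol itself fixes.

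A second reply is that the consequence is small and in the safe direction. This stands in full. At SD 0 to 0.2 the power difference is 0 to 0.2 points. SDs of 0.4 and above imply wide spreads in centre rates, for which the protocol offers no evidence.

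Three stronger readings are tempting and unsupported:
- A reader might infer that two tests are each judged at 0.049, so that the error rate is inflated. The text does not say so, and step 4 shows that even an either-test rule would add essentially nothing.
- A reader might infer that the sample size is wrong. It reproduces, and it is adequate for the stratified test.
- A reader might want BMI, lowest pulsatility index and notch status added to the model for more power. Section 12.4 plans adjustment for stratification factors only. The women are already selected on pulsatility index and/or notch, and the protocol gives no figure from which to estimate a gain.

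**Conclusion.** The point holds as a modest mismatch between design and analysis, joined to an incomplete specification. The apparent main test ignores the only stratification factor, and the thresholds and interim-adjusted results are not tied to a named analysis.

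The cost depends on an assumption the protocol cannot settle. It is nil or negligible at a logit SD of 0 to 0.2, about 0.6 to 0.7 points of power at 0.4, 1.5 points at 0.6 and 2.7 points at 0.8. These figures assume exact balance within centre, the centre sizes forecast in section 19 and a single look. Neither the type I error nor the sample size is compromised. The change is worth making because it uses precision the design already provides and removes an avoidable choice at each look.

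**What to change.** In section 12.4, name the Cochran-Mantel-Haenszel test stratified by investigating centre as the single test of the primary endpoint, applied at 0.001 at each interim analysis and at 0.049 at the final one. State that the effect estimate, confidence interval and p-value adjusted for the interim looks come from this same centre-stratified analysis, with the effect scale named in advance. Label the plain chi-square and the centre-adjusted logistic model as supportive.

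The cost is a few sentences in the protocol, carried into the statistical analysis plan. Centre is already known for every woman, the 4,972 inclusions stand, and nothing extra has to be collected. Like any change to the main analysis, it should be made without reference to unblinded results.

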### First trimester Doppler ultrasound

For this reason, many teams turned to first trimester screening [25-27]. This development goes hand in hand with the development between 11 and 14 WA of screening policies in other areas such as that of Down syndrome, for example (measurement of foetal neck).

Unlike during the second trimester, changes in uteroplacental circulation between 11 and 14 WA are still only very partial, the invasion of the spiral arteries by trophoblast cells being incomplete or even only beginning. It is therefore understandable that the performance of the Doppler ultrasound of the uterine arteries is weaker. Thus, in a large study involving 3,324 non-selected patients, the value of a pulsatility index (PI) ≥ 95th percentile gives only a sensitivity not exceeding 27% for the screening of pre-eclampsia (60% for early onset and severe pre-eclampsia requiring extraction before 32 WA) and 11.7% for the screening of IUGR (27.8% for IUGR requiring extraction before 32 WA) [26]. If a lower specificity value is allowed (10% false positives), sensitivity increases, in this same population, to 52% [22].

Recently, several publications have pointed out that, instead of focusing on the average PI of the two uterine arteries, which can be influenced by the lateralisation of placental insertion, it is the lowest PI on the side where the placenta is implanted that has the highest sensitivity value, mainly for early pre-eclampsia [28-30]. It is relatively difficult to give an upper-bounding threshold of this lowest PI between right and left uterine arteries. However, in a study of more than 9,000 low-risk singleton pregnancies, with a pre-eclampsia prevalence of 2%, the median (interquartile range) of the lowest PI was 1.68 (1.24-2.16) for patients who developed pre-eclampsia versus 1.4 (1.14-1.72) for patients who were not affected [30]. For patients developing early onset pre-eclampsia, this value was 2.26 (1.82-2.41). Based on this broad study, a low PI threshold ≥ 1.7 seems to have a good discriminating value since it concerns less than 25% of patients who will not develop pre-eclampsia and more than 50% of those who will progress to PE (more than 75% of those who will have early onset pre-eclampsia).

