# Research endpoints

## Primary endpoint

Occurrence of pre-eclampsia during pregnancy or birth weight ≤ 5th percentile:

- Pre-eclampsia, defined as gravid arterial hypertension and proteinuria after 20 WA or in the postpartum period. Arterial hypertension is defined as a systolic blood pressure ≥ 140 mmHg and/or a diastolic pressure ≥ 90 mmHg, measured twice and separated by at least 4 hours. Proteinuria is positive if it is greater than 500 mg/L.
- A birth weight ≤ 5th percentile for the gestational age on AUDIPOG curves adapted to the sex of the newborn and the maternal body mass index (individual curves) [40].

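### The only adjusted primary analysis uses centre alone in a logistic model; adding baseline values the trial already has, and reporting on the risk scale, is a cheap but modest gain

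*Protocol*

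**What the plan says.** Protocol 12.4 (Primary endpoint analysis) compares event rates with a chi-square test and adds: "An adjustment for stratification factors will also be made as part of a logistic regression model". Section 8.1.2 (Randomisation) gives one stratification factor, the investigating centre. No other covariate and no effect measure is named.

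The same document describes baseline values that are not in this model:

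- **Lowest PI.** It is one limb of the and/or Doppler criterion in 9.1. Section 10.1.1 has each woman receive "a duplicate of the Doppler images of each uterine artery" so that eligibility can be checked at the inclusion visit. Section 2.5.2 reports, from a large study of low-risk pregnancies, that "the median (interquartile range) of the lowest PI was 1.68 (1.24-2.16) for patients who developed pre-eclampsia versus 1.4 (1.14-1.72"; the last bracket is the interquartile range in unaffected women.
- **Maternal BMI.** Section 7.1 scores birth weight on curves "adapted to the sex of the newborn and the maternal body mass index". Section 2.7 lists obesity among the risk factors.
- **Gestational age.** Section 9.1 limits it at entry, and 12.5 plans subgroup analyses by gestational age and BMI.

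The sizing in 12.1 is on the risk scale: "Our hypothesis is that aspirin will reduce the occurrence of events by 15" per cent, that is, "21.2% of events are expected in the control group compared to 18.0% in the experimental group".

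**The concern.** In a sample of this size, adjusting for a prognostic baseline variable and standardising to a risk difference does not lose precision asymptotically, and it gains in proportion to the outcome variance explained. The protocol argues that PI is informative and then leaves it out of the one adjusted model it specifies. BMI must be collected anyway to score the endpoint.

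There is also a question of scale. The hypothesis is a relative reduction in risk and a 3.2-point difference. A logistic model gives an odds ratio, which lies further from 1 than the risk ratio when about a fifth of women have the event. What is at stake is a little precision and an adjusted estimate that answers the question the trial was sized for.

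**Working it through.** **Inputs from the protocol (12.1, 12.4).** Control 21.2%, aspirin 18.0%; type I error 5% (taken as two-sided, which reproduces the stated figure), power 80%; inflation factor 1.024; 0.5% of women not analysable; final threshold 0.049.

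**Reproducing the plan's figure.** With p1 = 0.212, p2 = 0.180 and mean 0.196:

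n = [1.960·√(2·0.196·0.804) + 0.8416·√(0.212·0.788 + 0.180·0.820)]² / 0.032² = (1.1003 + 0.4721)² / 0.001024 = 2415 per group.

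This matches "Considering the risks of type 1 and 2 errors set at 5 and 20% respectively, we must include 2415 women per group". Then 2415 × 1.024 = 2473, and 2473/0.995 = 2486 per arm. At 2473 per arm and 0.049, the unadjusted power is 80.7%.

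**What adjustment would add.** For a standardised risk difference, variance scales by about (1 − R²), where R² is the share of outcome variance explained by the covariates. The effective size is 2473/(1 − R²) per arm. The documents give no R² for the composite in randomised women, so it is an assumption:

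| Assumed R² | Effective n per arm | Extra women per arm | Power at 0.049 | 95% CI half-width (points) |
|---|---|---|---|---|
| 0% | 2473 | 0 | 80.7% | 2.21 |
| 1% | 2498 | 25 | 81.1% | 2.20 |
| 2% | 2523 | 50 | 81.5% | 2.19 |
| 3% | 2549 | 76 | 81.9% | 2.18 |
| 5% | 2603 | 130 | 82.7% | 2.16 |

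The power column applies if the adjusted estimate carries the conclusion. If the chi-square test decides, only the interval column is gained.

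**Comparison with the interim-look cost.** The protocol states that "the inflation parameter is 1.024", which is 2473 − 2415 = 58 women per arm, or 116 in all. Offsetting it needs R² = 58/2473, about 2.3%.

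**How much PI could explain after selection.** A simulation drew PI from the medians and quartiles in 2.5.2 (log-normal or normal). All women with PI ≥ 1.7 entered, and others entered through the notch, at rates that match the 75% and 55% sensitivities and 67% specificity in 12.1. It selected about 37% of women with an event rate of about 21%, close to the protocol's own figures.

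- A single linear PI term explained roughly 0-3.5% of the composite. The top of that range required PI to predict hypotrophy as strongly as pre-eclampsia. A separate run with a single log-PI term gave under 0.5%.
- Flexible terms explained more: about 2.5-3% for a quadratic in one run, and about 5-12% with fine grouping in another. Part of this reflects how selection was modelled, because women below 1.7 enter only through the notch. The upper figures should not be relied on.

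**Scale.** Risk ratio = 0.180/0.212 = 0.849. Odds ratio = (0.180/0.820)/(0.212/0.788) = 0.2195/0.2690 = 0.816.

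**The case against.** The strongest reply is that nothing here is wrong. The chi-square test compares rates, which is the scale of the sizing. The sample size assumes an unadjusted test and reproduces exactly. The trial keeps its planned power without PI. Section 12.2 announces a separate analysis plan, not shown here, which may name further covariates and an effect measure. All of this stands, except that 12.4 itself fixes the adjustment set and model type, so what it fixes can be improved.

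The evidence for PI is also limited. The quartiles in 2.5.2 come from low-risk women not selected on Doppler and concern pre-eclampsia only. For growth restriction the same section reports 11.7% sensitivity for a PI at or above the 95th percentile. Trial entry selects on PI itself, and the protocol does not say that the PI value is recorded for every woman. For BMI, the birth-weight curves already allow for it, and 2.7 says the non-obstetric risk factors concern few patients. No document quantifies what BMI or gestational age would add. These points stand and keep the expected gain small.

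A reader might infer that PI is a strong predictor and that adjusting for it must recover at least the cost of the interim looks. The documents do not support this: the break-even R² of about 2.3% is an assumption, and a single linear term may fall well short of it. A reader might also infer that the trial would report an odds ratio as an 18% risk reduction, but the protocol never names the odds ratio as its effect measure. Finally, adding PI to the logistic model alone would change the conditional odds ratio without narrowing its interval; the precision gain comes with standardisation.

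**Conclusion.** The primary analysis is valid and delivers its planned power. The point that holds is narrower: the one adjusted model in 12.4 uses centre only and is logistic, while the lowest PI, maternal BMI and gestational age at inclusion are measured or needed by the trial and are left out.

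The likely benefit is modest: from none to about 2 points of power for an assumed R² of 0-5% (80.7% to at most about 82.7%), or a confidence interval half-width of 2.16 rather than 2.21 points at best. It depends on how PI enters the model. The scale point needs no R² assumption: the planned effect is a risk ratio of 0.849 and an odds ratio of 0.816, and the adjusted result should be given on the scale used for sizing. This is a low-cost improvement to a stated rule, not a defect that threatens the trial's conclusion.

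**What to change.** Amend 12.4 before the first interim look so that:

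- the adjusted model contains, besides centre, the lowest PI as a flexible term (for example a quadratic or spline on the log scale), route of entry (notch, PI or both), maternal BMI and gestational age at inclusion;
- any missing covariate is filled by simple imputation, so that no woman is dropped;
- the result is reported as a standardised risk difference and risk ratio with confidence intervals;
- the text says whether the chi-square test or the adjusted estimate carries the primary conclusion.

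If the separate analysis plan already does this, 12.4 need only refer to it. The cost is analysis wording and one field in the electronic case report form if the PI value is not already recorded. No extra patients or procedures are needed.
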